**Fig. 1 Fig1:**
[figure not shown]
Schematic of the cross-over study design. Interested individuals will first perform an eligibility assessment to determine whether they can be consented into the study. Once 35 residences have been recruited (between 35 and 70 participants), participants will be randomized into two cohorts and experience three lighting conditions (L1, L2, L3). Lighting conditions are described in more detail in the “Environmental Lighting Conditions” section

Before starting the first lighting condition (L1 or L2 depending on the cohort), a baseline period lasting approximately 2 weeks will be used to characterize the lighting quality of each participants residence. The lighting in the baseline period will be set to match as closely as possible the lighting that was previously installed. Throughout the baseline, participants will be instructed to use the light as they normally would.

The L1 lighting condition and the baseline condition will have the same lighting parameters and will be configured to match the residents existing lighting prior to installing the current lighting system. Participants will be instructed to keep the lights all the time while awake during the duration of the study, however we gave individuals flexibility to wake up when they naturally did to not disrupt their sleep patterns by shifting to a rigid wakeup schedule.

After each 4-week lighting condition of the cross-over design, participants will experience a 1-week “washout” period during which they will experience the same lighting as the baseline period (L1 condition). After completing the cross-over and subsequent washout period, participants will experience the L3 condition to determine if there is a saturation effect of how much morning blue-rich light is needed to affect the health-related measures of interest.

### Measures of brain health using wearable devices

The goal of this study is to assess how lighting affects different measures of brain health. Although we are not performing any neuroimaging to directly measure brain activity, we are able to use different wearable devices, cognitive assessments, and surveys to infer how measures of brain health change, including changes in participants cognitive, mental, and physical health. During each day of the study, physiological measures will be recorded using wearable devices. Heart rate, steps taken, and sleep quality will be measured using a wrist-worn smartwatch (Withings ScanWatch, Withings, France SA). Participants will be asked to wear the smartwatch when awake and asleep, except when needing to bathe, wash, or swim, or when they need to charge the device. Measurements that will be analyzed from the watch will include participants’ steps taken and heart rate throughout each day of the study. Under-the-mattress devices (Withings Sleep Tracking Mat) will also be used to monitor each participant’s sleep. In combination with the smartwatch, sleep measurements that will be analyzed will include participants’ total sleep time, wake after sleep onset, and sleep stages (deep sleep, light sleep, and probable REM sleep as reported by the device). Data from these devices will be synchronized using the Withings Health Mate App (Withings, France SA).

Participants will also wear a LYS light sensor (LYS Technologies LTD, Copenhagen, Denmark) to monitor the amount of light to which they are exposed each day. Each participant will wear the LYS sensor on their collar to best capture their personal light exposure as close to their eye level as possible. This device will capture their light exposure both within and outside of their residence. The LYS button will measure EML, illuminance (lux), and correlated color temperature (CCT) which will be compared across each day of the study. To ensure compliance that participants wear the device, we can monitor the recorded values remotely each day. Should the signals recorded have very low variance, we will use this as an indicator to have a member of the study team reach out to the participant to ensure they are wearing the device.

These devices are commercially available and designed with safety in mind. Participants will be shown how to use each of the devices before the start of the study and will be encouraged to submit any questions to the study coordinator throughout the study.

### Measures of cognitive performance

The goal of analyzing cognitive performance using these tablet-based assessments is to assess how cognitive performance changes in a short time frame (i.e., how cognitive performance changes in each 4-week lighting condition). Due to the time constraints of this study design, we are unable to accurately assess changes in longer-term cognitive performance (e.g., cognitive slowing), however findings from this study could serve as preliminary indicators upon which a longer duration study could be performed. We will use tablet-based cognitive assessments to measure key aspects of executive functioning including working memory, response inhibition, and task switching. These assessments were designed around existing, validated cognitive assessments and were created in a custom-built application designed in the Well Living Lab.

Attentional control will also be assessed using a reaction time task. To capture individual differences in working memory, participants will perform the Operation SPAN task in which sequences of letters are remembered while also performing a distractor task comprised of mental math problems [77]. For the response inhibition dimension of executive functioning, participants will perform a classic three-color Stroop task in which participants indicate the font color of a color word while ignoring the word meaning (e.g., the word “red” in green font) [78]. To capture the task switching dimension, participants will complete a magnitude/parity task in which participants complete two different tasks based on the color of a number presented. If the number is yellow, participants indicate whether or not the number is larger than 5, and if the number is purple, participates indicate whether the number is even or odd. For the reaction time task, participants will perform the psychomotor vigilance task (PVT), which is a sustained-attention, reaction-timed task that measures the speed with which subjects respond to a visual stimulus [79].

Shortened versions of these tasks will be administered electronically on an iPad provided to the participants. Each task is expected to take approximately 5–10 min to complete, including a 1-minute training block that will be completed prior to each task throughout the study. Performance of these tasks will be assessed via accuracy, response latency, and overall duration to complete each task. These metrics will be compared across the different lighting conditions to understand how cognitive performance changes during the study.

Participants will be provided a schedule of when these assessments will be delivered throughout each week of the study and will be asked to perform these assessments in the morning (between 8am-12pm). Participants will be asked to perform assessments 2 times per week. Each participant will be able to access a customized webpage where they can check in to see which assessments they need to complete each day. Prior to study launch, a study team member will provide in-person instruction for completing these assessments. Compliance will be monitored remotely by the study team and participants will be reminded if they fail to complete multiple assessments.

### Self-report measures (surveys and questionnaires)

Participants will be asked to complete surveys and questionnaires to obtain self-report measures of sleep quality, social engagement, cognitive function, depression, and mood throughout the study. Surveys will be deployed electronically using Qualtrics and will include sleep questionnaires (Groningen sleep survey, Berlin Questionnaire, Stanford Sleepiness Scale (SSS) [80], and/or the Morningness Eveningness Questionnaire) [81], social engagement questionnaires (Lubben Social Network Scale [82], UCLA Loneliness Scale [83]). Participants will also complete mood- or depression-related questionnaires including the Patient health Questionnaire (PHQ8) [84], the Depression Anxiety and Stress Scale (DASS-21) [85] the Scale of Positive and Negative Affect (SPANE) [86], independence surveys (Lawton-Brody IADL Scale) [87], and the Ten Item Personality Inventory (TIPI) [88].

Similar to the cognitive assessments, surveys will be displayed on the same customized webpage and monitored by members of the study team to ensure compliance. A one-time baseline survey will be administered at study onset which will capture characteristics that are not expected to change over the course of the study (see Table 1 for the full survey schedule). Next, a brief (approximately 2–3 min) daily survey will capture changes over the previous 24 h. A weekly survey will be administered to capture other processes that may change over the course of a week (e.g., PHQ8, UCLA loneliness scale). Another survey will be administered at the end of each condition to characterize changes that might occur more slowly during each condition (e.g., Lubben Social Network Scale). Participants will also be asked to fill out a brief qualitative survey about each lighting condition they experience (e.g., “End of Condition” Survey). To ensure participant compliance for completing the surveys, we are able to monitor their survey performance remotely using a custom-built dashboard. By ensuring that each survey is completed (such as within 24 h of when they are delivered), we can reach out to participants who might forget to complete the assessments (see Data Auditing and Compliance section below).

**Table 1 Tab1:** The list of surveys administered and when they are administered to each participant during the study

Survey	When Administered
Eligibility/Screening Survey	Before consent
Medical History	After consent
Socioeconomic survey	After consent
Morningness Eveningness Questionnaire (MEQ)	Start of Baseline
Berlin Questionnaire	Start of Baseline
TIPI Big 5 Personality	Start of Baseline
Stanford Sleep Scale	Daily
SPANE	Daily
Groningen Last Night Sleep Report	Daily
DASS21	Weekly
PHQ-8	Weekly
UCLA Loneliness Scale	Weekly
Falls / Hospitalization Survey	Weekly
Lawton Brody Instrumental Activities of Daily Living Scale	End of Condition
Lubben Social Network Scale - Revised (LSNS-R)	End of Condition
End of Condition Survey	End of Condition
End of Study Opinion Survey	End of Study

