### Statistical analysis plan

Using data from both wearable devices and surveys, the primary comparison will be within-person change in sleep quality scores between each of the three lighting conditions (L1, L2, L3) and the same scores measured during the baseline period. The L1 condition serves as an active control condition as this is the same lighting as they would typically experience in the baseline condition. The secondary comparison will be to compare changes in physical activity, heart rate, and survey data across each lighting condition pair. Data collected during the baseline period will also be compared against the L1 condition to determine whether asking participants to change their behavior with the lights (e.g., do not turn the lights off) affects any of the dependent variables of interest, thereby ensuring that any health benefits seen in the dynamic conditions relative to the static condition are likely reflective of improvements over participants lighting as usual. Participants who are eligible only because their partner is eligible will be analyzed separately.

We will use generalized estimating equations to account for the longitudinal repeated-measures design and handle missing data. For the surveys and cognitive assessments, there will be a minimum of 8 measurements per lighting condition (two cognitive assessments per week for four weeks). If only 35 participants are enrolled, we expect 80% power to detect a difference of minimum of 0.45 standard deviations. Conversely, if we have 70 participants enrolled (i.e., all the rooms are double occupancy with both persons eligible) we expect 80% power to detect a minimum difference of 0.3 standard deviations. For either of these scenarios, we expect to be able to detect at least 0.3 standard deviations, yielding sufficient power, even for the relatively infrequent cognitive assessments. To minimize missing data,, we will monitor key metrics (such as response rates) throughout the study using IRB-approved approaches to encourage participation. As a rule of thumb, participants who complete the study with greater than 50% missing data on any outcome measure will not be included in the relevant final analysis population.

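### As Table 1 stands, the LSNS-R and Lawton-Brody scales have no baseline value, so the planned baseline-versus-L1 check cannot be run for them

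*Protocol article*

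**What the plan says.** The section on self-report measures sets out four survey frequencies: once at baseline, daily, weekly, and at the end of each condition. For the last it says: "Another survey will be administered at the end of each condition to characterize changes that might occur more slowly during each condition", with the Lubben scale as its example. It refers the reader to Table 1 as complete: "see Table 1 for the full survey schedule".

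The relevant rows of Table 1 are:
- "Lubben Social Network Scale - Revised (LSNS-R) End of Condition"
- "Lawton Brody Instrumental Activities of Daily Living Scale End of Condition"
- "TIPI Big 5 Personality Start of Baseline", a time point shared only with the MEQ and the Berlin Questionnaire.

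The baseline survey is limited to stable traits: "A one-time baseline survey will be administered at study onset which will capture characteristics that are not expected to change over the course of the" (quote cut before its last word).

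The Statistical analysis plan section adds a check on the active control: "Data collected during the baseline period will also be compared against the L1 condition to determine whether asking participants to change their behavior". The behaviour meant is how they use their lights, and the check asks whether the instruction has an effect on any outcome under study. Its stated purpose is to support reading a benefit of dynamic over static lighting as a gain over the resident's usual lighting.

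**The concern.** L1 and baseline share the same lighting settings. They differ in that participants use their lights as usual during baseline and are asked to keep them on while awake during L1. The baseline-versus-L1 comparison is how the protocol separates the effect of that instruction from the effect of the lighting, and the Discussion presents it as an innovative part of the design.

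The check needs a value from the baseline period, and Table 1 shows none for the LSNS-R or the Lawton-Brody scale. The LSNS-R matters more, because it is one of the two scales listed for social engagement, a named secondary outcome. The Lawton-Brody scale measures independence, which is not among the named secondary outcomes. If no baseline score is collected, no later analysis plan can supply one.

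There is also a wording problem. The article says the end-of-condition survey captures change during a condition, but a single score at the end gives a level.

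**Working it through.** The point concerns the assessment schedule, so the check is a count of administrations along the timeline. The plan states no figure for these scales that could be reproduced.

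**Inputs**
- Baseline of about 2 weeks; three conditions of 4 weeks each; a 1-week washout at L1 lighting after each of the two cross-over conditions (study design section).
- Cohort 1 order: L1, L2, L3. Cohort 2 order: L2, L1, L3 (same section).
- Both scales at the end of each condition only (Table 1).

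**Timeline**

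2 + 4 + 1 + 4 + 1 + 4 = 16 weeks, which matches the 16-week duration in the Abstract.

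| | Baseline (weeks 0-2) | Week 2 + 4 = 6 | Week 6 + 1 + 4 = 11 | Week 11 + 1 + 4 = 16 |
|---|---|---|---|---|
| Cohort 1 | none | end of L1 | end of L2 | end of L3 |
| Cohort 2 | none | end of L2 | end of L1 | end of L3 |

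Each scale has 3 scores per person and 0 in the baseline period.

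**What can be computed from these scores**
- L1 versus L2 (central hypothesis): yes, from end-of-condition scores in both cohorts.
- L2 versus L3 (secondary hypothesis): yes, likewise.
- Baseline versus L1: no, for any participant in either cohort, because the baseline term is missing.
- Change within the first condition: no, because there is no start value.
- Change within the second or third condition: not cleanly. The nearest earlier score is from the end of the previous condition, before a week of washout.

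**With one administration at the end of baseline**

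Each person would have 3 + 1 = 4 scores. Baseline versus L1 and change over the first condition become computable in both cohorts. The second and third conditions still lack a clean start value, because the washout comes between.

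**The case against.** The strongest reply is that the label may already cover baseline. The article speaks of a baseline condition twice, once in the study design section and once in the Statistical analysis plan section. On that usage an end-of-condition survey could fall at the end of baseline, and the start-of-baseline label would simply mark a different moment. This stands as a possibility. Against it, the study design section counts three lighting conditions, and nothing in Table 1 places either scale in the baseline period. A reader might infer that the article proves these data will never be collected. It does not go that far; it leaves the missing baseline score as the natural reading.

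A second reply is that the check promises less than it seems to. Its sentence can be read as covering whatever is collected at baseline. The primary comparison with baseline is for sleep quality, survey data are to be compared between pairs of lighting conditions, and the Discussion describes the baseline comparison in terms of recorded activity. This has some force, but the section names its target as any outcome under study and exempts no scale.

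A third reply is that giving slow-moving scales only at the end of each period is a defensible choice in a cross-over where participants are their own controls. That is right for the two hypothesis tests, neither of which needs a start value.

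**Conclusion.** The point holds in a limited form. On the natural reading of Table 1, the baseline-versus-L1 check cannot be run for the LSNS-R or the Lawton-Brody scale in any of the 35 to 70 participants. This rests on the end-of-condition label meaning the end of L1, L2 and L3 only.

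Two stronger conclusions are tempting and not supported:
- That the treatment comparisons for these scales are damaged. The L1-L2 and L2-L3 contrasts use end-of-condition scores and are unaffected.
- That social engagement loses its active-control check altogether. The UCLA Loneliness Scale is weekly and can support the check if it is given during baseline; Table 1 does not say whether the weekly surveys run then.

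What remains is a gap in an auxiliary check. In practice it concerns one of two social-engagement scales, together with a description of change during each condition that the schedule does not deliver. It is a cheap improvement, not a threat to the trial's main conclusions.

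**What to change.** In Table 1, schedule the LSNS-R and the Lawton-Brody scale once at the end of baseline, in addition to the end of L1, L2 and L3. The end of baseline is preferable to its start because it matches the timing of the later scores. If the end-of-condition label was already meant to include baseline, one added line in the table settles it.

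If baseline has already passed, which is possible given the December 2023 target for completing recruitment in the Trial status section, state in the Statistical analysis plan section that these two scales are exempt from the baseline-versus-L1 check.

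In either case, describe both scales as end-of-condition levels compared between conditions, not as change during each condition. The added baseline score does not give the second and third conditions a clean start value, so that wording would remain wrong without this edit.

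The cost is two short electronic questionnaires once per participant, or a wording change only if baseline is over.

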### Data auditing and compliance

All incoming data streams will be continuously monitored by the research team for missingness using cloud-based APIs and real-time database visualization queries. Participants who possess devices with more than 48 h of missing data will be contacted for troubleshooting, and study representatives will support participants as needed. Participants missing 3 out of 4 days or 3 consecutive daily surveys will be contacted with offers to support. Repeated failures to complete study tasks will involve the study’s primary investigator (PI) reaching out to participants to develop a personalized strategy to increase compliance.

### Mental health mitigation plan

Some of the surveys being proposed to use in the study (such as the PHQ8) can be used as a diagnostic tool and as such require a mental health risk mitigation plan. The same research coordinator responsible for cohort allocation will monitor the scores from this survey each time it is administered for each participant (weekly). At the start of the study, contact information will be collected for each participant’s primary care physician (PCP). If a participant scores as having severe depression on the inventory (PHQ score > = 20), the research coordinator will notify the PI ([name]) who will then inform the participant and their PCP of the reported severe depression levels. If the depressive episode has not been previously diagnosed or treated, the PCP will be asked to follow up with the participant to discuss changes in their mood and create a response plan. Participants will subsequently be asked whether they would like to continue with the study. If they are interested in continuing, the participant will again complete the UBACC consent capacity protocol (previously discussed) to ensure that they are able to consent. This procedure will also ensure that the participant fully understands their option to leave the study at any time.

### Measures of clinical events

The intervention proposed here is non-intrusive and not anticipated to elicit any adverse events. Participant adverse events may include adverse reactions to the lighting conditions in the room, falls, hospitalizations, etc. All adverse events that occur during this study will be recorded and documented. Because this is an exploratory study, the full extent of adverse events is unknown and all events occurring during the duration of the study will be recorded and analyzed. Adverse events could typically happen with the older participant population independent of this study. We will electronically send a form to each participant every 2 weeks throughout the study to ascertain if any adverse events, such as a fall or hospitalization, has occurred. Comparing the incidence of adverse events documented during the study with historical adverse events incidence rates (such as those reported in the Mayo Clinic Olmsted Study of Aging [89] will help us identify clinical benefits to the proposed lighting conditions. If participants identify any adverse event related to the lighting conditions, wearable devices, or other study procedures, the research team will contact the participant and clearly re-iterate that study participation is fully voluntary and that participants can leave the study at any time for any reason.

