### Study design: cross-over study design with an exploratory third condition

The present study employs a two-arm, randomized, cross-over, single-site trial design. Participants will experience three 4-week lighting conditions (indicated as L1, L2, and L3 and described in the “Environmental Lighting Conditions” section to follow and depicted in Fig. 1). Cohort 1 will experience L1 followed by the L2 condition and cohort 2 will experience L2 followed by the L1 condition. Both cohorts will then experience the L3 condition. The primary outcome of this study is to determine how each lighting condition affects measures of sleep quality as assessed using wearable devices and self-report surveys. The secondary outcomes of this study are to determine how each lighting condition affects physical activity, cognitive function, social engagement, and mood as assessed using wearable devices, cognitive tasks, and self-report surveys. We will compare each of these measures between the L1 and L2 condition to test our central hypothesis that exposure to dynamic lighting (L2) will result in improvements of each measure compared to static lighting (L1). We will then compare these measures between L2 and L3 conditions to test our secondary hypothesis that improvements in measures of brain health saturate based on the amount of equivalent melanopic lux (EML) exposure.

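### Comparing adverse-event incidence with historical rates cannot identify a clinical benefit of the lighting; events should be reported by condition, and the two stated reporting intervals reconciled

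*Protocol article*

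**What the plan says.** Under Measures of clinical events, the Protocol article says that all adverse events, including falls and hospitalisations, will be recorded and analysed. It then gives one use for them: "Comparing the incidence of adverse events documented during the study with historical adverse events incidence rates", with a regional ageing study as the example source, "will help us identify clinical benefits to the proposed lighting conditions". That section mentions no comparison between lighting conditions.

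The design section sets up a randomised comparison: "Cohort 1 will experience L1 followed by the L2 condition and cohort 2 will experience L2 followed by the L1 condition". Both cohorts then receive L3. The Statistical analysis plan section adds: "The L1 condition serves as an active control condition". It also plans to compare survey data across pairs of conditions, without naming falls, hospitalisations or adverse events. These events are not among the secondary outcomes listed in the design section.

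Two reporting intervals are given. Measures of clinical events says: "We will electronically send a form to each participant every 2 weeks throughout the study to ascertain if any adverse events" (falls and hospitalisations are its examples). Table 1, under Self-report measures, lists the "Falls / Hospitalization Survey" as weekly.

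**The concern.** A difference between the study's event rate and an external rate has several possible sources besides dynamic lighting:

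- **Selection.** Participants live independently, pass a consent-capacity test, are not legally blind and do not plan to be away for more than a week. The Discussion concedes that residents' demographics and co-morbidities may not match the wider population.
- **Ascertainment.** Participants are asked about events every week or two. The article does not say how the historical rates were collected.
- **Co-intervention.** In all three conditions participants are to keep the lights on while awake. The Background describes more ambient light as a way to lower fall risk. L1 is the active control that separates this behaviour change from dynamic lighting; a historical comparator does not.
- **Mixed exposure.** Half of the scheduled time uses L1-type lighting.

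A reader could therefore credit the lighting with a difference that it did not cause, or miss one that it did. The conflict over the interval matters because the washouts last one week. A 2-week recall window cannot fit inside one.

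**Working it through.** **1. Timeline.** The inputs are a baseline of about 2 weeks, three 4-week conditions, and a 1-week washout after each cross-over period (Study design section). The sum is 2 + 4 + 1 + 4 + 1 + 4 = 16 weeks, which reproduces the 16 weeks stated in the Abstract. The calendar is: baseline weeks 1–2, period 1 weeks 3–6, washout week 7, period 2 weeks 8–11, washout week 12, L3 weeks 13–16.

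**2. Share of L1-type lighting.** Baseline and washouts use the L1 lighting parameters. Each participant therefore has 2 + 4 + 1 + 1 = 8 weeks of L1-type lighting and 4 + 4 = 8 weeks of dynamic lighting.

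**3. Dilution of a study-wide rate.** Assume the historical rate equals the participants' own rate under L1-type lighting, and that L2 and L3 share the rate ratio RR. The apparent ratio is then (8 + 8 × RR)/16.

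- RR = 0.7: (8 + 5.6)/16 = 0.85
- RR = 0.5: (8 + 4)/16 = 0.75
- If only the 12 weeks of the three conditions are pooled, RR = 0.7 gives (4 + 8 × 0.7)/12 = 0.80

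**4. What a non-comparable historical rate does.** Let participants' underlying rate be k times the historical rate. The apparent ratio is k × (8 + 8 × RR)/16. With no lighting effect (RR = 1), k = 0.85 gives 0.85, the same result as a true RR of 0.7 with k = 1. In the other direction, k = 1/0.85 = 1.18 with RR = 0.7 gives 1.00 and hides the effect. The documents do not give k, so the comparison cannot tell these cases apart.

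**5. Reporting windows on the calendar.**

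| Schedule | Windows crossing a period boundary |
|---|---|
| Weekly, aligned | 0 of 16 |
| 2-weekly from study start | 2 of 8 (weeks 7–8 and 11–12) |
| 2-weekly, shifted by one week | 3 of 8 (weeks 2–3, 6–7 and 12–13) |

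With windows from study start, both crossing windows join a washout week to a week of period 2. In cohort 1, period 2 is L2, so L1-type lighting is mixed with L2, and 2 of the 4 L2 weeks (8 and 11) lie in mixed windows. In cohort 2, period 2 is L1, so the lighting parameters are the same on both sides.

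**6. What the randomised contrast can deliver.** Person-time per condition, with full follow-up, is 35 × 28/365.25 = 2.7 to 70 × 28/365.25 = 5.4 person-years. The article gives no event rate. At an assumed 0.1 to 1.0 events per person-year, about 0.3 to 5.4 events are expected under L1. For 80% power at two-sided 5%, the approximate total needed is 4 × (1.960 + 0.842)² / (ln RR)². That is 247 events for RR = 0.7 and 66 for RR = 0.5. Simulated power for L1 versus L2 (Poisson counts, exact conditional test) was below 8% in every scenario tried: 35 or 70 participants, 0.1 to 1.0 events per person-year, RR 0.7 or 0.5.

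**The case against.** The article says only that the historical comparison will help to identify benefits. Falls and hospitalisations are neither primary nor listed secondary outcomes, the section calls the study exploratory, and no test rests on them. This limits the weight of the point but does not make the inference sound.

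A reader might infer more than the documents support in four places:

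- **That the plan ignores its randomised control for these events.** The Statistical analysis plan section compares survey data across condition pairs, and the falls survey is one of the surveys in Table 1, so an L1–L2 comparison may already be intended. What stands is that the section on clinical events names only the historical comparator.
- **That rates will be pooled over the whole study.** Incidence during the study is most naturally read that way, but rates by condition are not excluded. The 0.85 applies only if the study-wide rate is used.
- **That a healthier sample would be reported as a benefit.** The direction of the selection difference is unknown, and active questioning could push the rate the other way.
- **That events in crossing windows cannot be assigned to a condition.** This holds only if event dates are not collected, and the article does not say. It also needs the 2-week schedule to govern, a baseline of exactly 2 weeks, and forms counted from study start. Under those conditions only cohort 1 is affected. Under the weekly schedule the problem does not arise.

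It is also fair to object that the L1–L2 contrast has almost no power. That is right, and it is why the contrast should be descriptive. It does not make the historical comparison informative.

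**Conclusion.** The point holds in a limited form. The article names a historical comparison as a way to identify clinical benefits of the lighting, and that inference is not supportable. It is open to differences in selection and ascertainment, it includes the effect of keeping the lights on, and a study-wide rate would be half control time. On that last count alone, a true rate ratio of 0.7 would read as 0.85. This assumes a perfectly comparable historical rate and equal effects of L2 and L3.

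The 2-weekly and weekly intervals conflict as written. If two separate instruments are meant, the article does not say so, and one event could then be counted twice. The effect on attribution to a condition depends on the assumptions set out above and falls on cohort 1's L2 period.

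The primary and listed secondary outcomes are not affected. The change is worth making because the wording invites a conclusion that the data cannot carry.

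**What to change.** In Measures of clinical events:

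- Report falls and hospitalisations per person-time by condition. Take L2 versus L1 within the cross-over as the reference contrast, with an estimate and confidence interval, labelled descriptive.
- Keep historical rates as context only and delete the statement that they help to identify clinical benefits.
- Reconcile this section with Table 1 to one reporting interval whose windows align with the condition boundaries. If two instruments are meant, say so and state how duplicate reports are handled.
- Record the date of each event.

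The cost is a change of wording, a date field and one small table. The downside is that, with 2.7 to 5.4 person-years per condition, the interval will be wide and no benefit on falls or hospitalisations can be claimed.
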